**Fig. 1 Fig1:**
[figure not shown]
Study area **A** location of Muheza District in Northeast Tanzania; **B** proposed clusters in Muheza District. The maps of Tanzania and Muheza district were produced using QGIS 3.22 software [44] and overlaid on Google Earth satellite images by the study investigator ([name]). Using QGIS 3.22 software [44], a one kilometre transect from the mid-point to the perimeter of each village was digitized to produce the shape files for the clusters in the Muheza map

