### Power calculation, estimation of effect size and cluster selection

Sample size calculations will be based on the study primary endpoint i.e., indoor density of *Anopheles* mosquitoes. An estimated mean of 3.0 female *Anopheles* per light trap per night will be used, referencing data from recent studies in Tanzania [27]. A paired design will be used in which clusters will be matched on baseline indoor density of *Anopheles* mosquitoes. Previous data suggests a within-pair coefficient of variation of 0.23, but a conservative value of 0.3 will be used in our calculations.

The trial is a non-inferiority design, intended to show that spraying the intervention product, VECTRON™ T500, will not result in higher malaria vector densities, by a prespecified non-inferiority margin of 50%, than those per trap per night in the reference arm sprayed with Fludora® Fusion. Using the methods described in Hayes and Moulton [28] and the assumptions listed above, it was calculated that 8 clusters per treatment arm (16 in total) will be needed for the 50% margin to have 80% power to demonstrate non-inferiority. The calculations were based on 49 trap nights per cluster. There was very limited statistical advantage in increasing trap-nights beyond 50. This number of clusters considers the loss of degrees of freedom caused by matching.

Sixteen clusters, containing 75–200 households per cluster (HHs), will be selected for spraying. Core areas of clusters should be at least 1 km apart to prevent infiltration of mosquitoes from other villages. All consenting HHs in all 16 clusters will be sprayed. Approximately 1200–3200 households will be sprayed (~ 75–200 HHs/cluster in 16 clusters).

Although a minimum of 49 households is required per cluster according to the sample size calculations, a larger hamlet will be recruited for logistical reasons, as a proportion of households may refuse to accept the IRS spraying and others may be absent during spraying or lost during follow-up.

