During baseline vector density monitoring, 20 clusters will be included, to improve the pair-matching post-intervention. The four clusters with greatest variance will not be included in the post-intervention monitoring but will still receive the IRS treatment. The 16 selected clusters will be pair-matched based on vector densities and randomly allocated to the two trial arms: one arm (8 clusters) will be sprayed with the novel intervention (VECTRON™ T500) and the other arm (8 clusters), the reference product (Fludora® Fusion). All possible randomisations will be stratified on ITN coverage and wall surface to ensure minimum difference of 15% or less in mean ITN coverage and mean ratio of cement houses to mud houses per arm. From all randomisations that meet these criteria, one will be selected at random.

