### Intervention monitoring

#### Vector density

CDC light traps hung inside houses next to occupied LLINs will be used to collect mosquitoes for species identification, sporozoite ELISA, and characterization of DNA-based resistance mechanisms. Four operatives will be allocated with 5 light traps each and given responsibility for trapping in 4 of the 16 clusters. In each cluster in each month there will be 3 rounds of light trap collections spaced over 3 weeks in 15 randomly selected HHs. Therefore, in each treatment arm of 8 clusters there will be 120 light trap nights in each month. All households in each cluster will be re-randomised at each monthly surveillance point. Therefore, in each cluster there will be 180 light-trap nights spread across the 12-month post intervention period, from which non-inferiority will be determined. All mosquitoes collected will be identified morphologically to genus and species complex level (*An. gambiae s.l.*, *An. funestus s.l.* and *Culex* spp.). Sub-samples taken from each cluster each month will be identified to species level using molecular diagnostic assays; numbers and proportions identified will depend on the total numbers caught.

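### The 1 km separation rule covers only cluster core areas, but trap houses for the primary endpoint are drawn from all households in the cluster

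*Protocol article*

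**What the plan says.** The separation rule is in the section on power calculation, effect size and cluster selection: "Core areas of clusters should be at least 1 km apart to prevent infiltration of mosquitoes from other villages". It names the threat and sets a distance, but only between core areas. The article does not define the core and gives no minimum distance between cluster edges. The same section treats the whole cluster: "All consenting HHs in all 16 clusters will be sprayed".

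Trap-house selection is in the Vector density section: "In each cluster in each month there will be 3 rounds of light trap collections spaced over 3 weeks in 15 randomly selected HHs". It adds: "All households in each cluster will be re-randomised at each monthly surveillance point". The resulting 180 trap-nights per cluster over 12 months are the data on which non-inferiority is judged. Neither this section nor Data analysis limits trapping or the primary comparison to the core.

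On cluster extent, the caption of Fig. 1 says that "a one kilometre transect from the mid-point to the perimeter of each village was digitized" to make the cluster shapes. The map itself is not shown. Four further clusters "will not be included in the post-intervention monitoring but will still receive the IRS treatment".

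**The concern.** The two rules apply to different sets of houses. The distance rule protects the core, while the endpoint is measured anywhere in the cluster. A trap house outside the core can therefore lie closer than 1 km to a cluster treated with the other product, which is the situation the rule is meant to avoid.

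Both arms are sprayed with active products. If mosquitoes caught near a boundary partly reflect the neighbouring product, each arm's mean density moves towards the other's and the ratio moves towards 1. In a superiority trial this costs power. In a non-inferiority trial it works in favour of a product that is truly worse.

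**Working it through.** **1. The plan's own sample size.** Inputs from the power section: mean 3.0 per trap-night, margin 50% (a difference of 1.5 per trap-night, or a ratio of 1.5), within-pair coefficient of variation 0.3, 49 trap-nights per cluster, 80% power. The article states no alpha; two-sided 5% (one-sided 2.5%) is assumed. The Hayes and Moulton matched-pair formula with equal true densities is

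c = 2 + (1.96 + 0.84)² × [(3 + 3)/49 + 0.3² × (3² + 3²)] / 1.5²

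= 2 + 7.85 × (0.122 + 1.62) / 2.25 = 8.08 per arm.

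This agrees with the stated 8. The formula has no term for contamination, so the planned size neither depends on this point nor allows for it.

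**2. What the distance rule permits.** Assume circular clusters of 1 km radius (suggested by the transect in Fig. 1, not stated) and a core of radius r km. With core edges exactly 1 km apart, cluster centres are 2r + 1 km apart, so the gap between cluster edges is 2r + 1 − 2 = 2r − 1 km. The share of area outside the core is 1 − r².

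| Core radius r | Gap between cluster edges | Area outside core |
|---|---|---|
| 0.7 km | 0.4 km | 51% |
| 0.5 km | 0 km | 75% |

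This shows what the wording allows, not what the actual layout is.

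**3. Effect of mixing on the ratio.** Let R be the true density ratio (new to reference) and m the share of each arm's catch that reflects the other arm's density. Then

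observed ratio = [(1 − m)R + m] / [(1 − m) + mR].

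At R = 1 this equals 1 for every m, so equal products produce no bias. At R = 1.5 and m = 0.10 it is (1.35 + 0.10)/(0.90 + 0.15) = 1.38.

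**4. Effect on the error rate.** Take a paired t-test on the log ratio with 8 pairs (7 degrees of freedom), one-sided 2.5% and margin log 1.5. With Poisson counts, 180 trap-nights and mean 3.0 (180 × 3 = 540 mosquitoes per cluster), the SD of the pair log ratio is √[2 × (0.3² + 1/540)] = 0.429, and the standard error is 0.429/√8 = 0.152. The probability of declaring non-inferiority comes from the noncentral t distribution with noncentrality (log observed ratio − log 1.5)/0.152.

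| Assumed mixing m | Observed ratio when true ratio is 1.5 | False non-inferiority rate |
|---|---|---|
| 0 | 1.50 | 2.5% |
| 2.5% | 1.47 | 3.3% |
| 5% | 1.44 | 4.3% |
| 10% | 1.38 | 6.9% |
| 20% | 1.27 | 15.4% |

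**5. Would a core-only frame be large enough?** Clusters may have as few as 75 households, and the power section requires at least 49. With evenly spread houses, a core of radius 0.7 km holds 75 × 0.49 ≈ 37 and one of 0.5 km holds 75 × 0.25 ≈ 19. Both are below 49. Covering 180 trap-nights would then take about 5 nights per house (180/37) or more than 9 (180/19).

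**The case against.** The strongest reply is that the core is mentioned once and never defined. It may simply mean the settled, sampled part of a village, in which case the 1 km rule already covers the trap houses. The rule is a minimum, the map is not shown, and real villages may be much further apart. The sentence on monthly re-randomisation mainly says that houses are redrawn each month. This is also a condensed article, and the full protocol may restrict trapping to the core.

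These points stand as limits. They mean that a reader might infer actual contamination, or near-adjacent trap houses in opposite arms, but the documents show neither; they show only that the stated rules permit it. They do not remove the mismatch, because the distance is set for one area and the sampling frame is described as another.

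The size also needs restraint. If a house midway between opposite-arm clusters is mixed at most about half and half, m = 20% needs about 40% of all trap-nights at such houses, and m = 10% about 20%. Isolated clusters, and those beside a same-arm cluster, contribute nothing. A reader might also infer that a clearly inferior product would pass easily, because a true ratio of 1.8 with 20% mixing appears as 1.41, inside the margin. That does not follow: the confidence limit, not the point estimate, must lie below 1.5, and in the model above this case is declared non-inferior only 5.3% of the time (1.05% at 10% mixing).

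Finally, core-only trapping can fall below the 49-household minimum in small clusters, so the remedy has to be qualified.

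**Conclusion.** The point holds in a limited form. As written, the separation rule and the trap-house frame do not cover the same houses, so some primary-endpoint trap-nights may fall within 1 km of a cluster sprayed with the other product. The bias, if any, is towards non-inferiority, and it arises only when the new product is truly worse. Its size cannot be determined from the documents. The rise from 2.5% to between 3.3% and 15.4% is illustrative: it rests on an assumed mixing share of 2.5% to 20% in every cluster, an assumed one-sided 2.5% level, Poisson counts and the planning coefficient of variation of 0.3. The lower part of that range is a modest inflation. This is not evidence that the trial is biased; it is an avoidable gap between the plan's safeguard and its endpoint.

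**What to change.** In the Vector density section, use the GPS coordinates and cluster boundaries already recorded at the census to draw the monthly trap houses only from each cluster's core. Define the core so that trap-eligible houses in opposite-arm clusters are at least 1 km apart. Spraying still covers the whole cluster, as planned.

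Where this leaves fewer than 49 eligible households, keep the full frame for that cluster. Report a sensitivity analysis of the primary endpoint limited to trap-nights at least 1 km from the nearest opposite-arm cluster. When measuring that distance, count the four sprayed but unmonitored clusters according to the product they receive.

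If core and cluster are the same area, say so, and apply the 1 km rule to the nearest households of neighbouring clusters.

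The cost is a filter on the sampling frame, with no new data collection and no additional clusters. The downside is fewer eligible houses and more repeat trapping of the same houses in small clusters.

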### Sensitisation, community and household consent

A meeting with district authorities (District Medical Officer, District Executive Director and District Commissioner) will be held at the beginning of the project to present the objectives and research activities. Meetings with community representatives and hamlet leaders will encourage adherence of inhabitants.

Community consent will be obtained from village leaders, individual verbal and written consent will be obtained from family heads and household members. All households within each community will be offered IRS.

The risks and benefits of participation will be made known and the opportunity to withdraw will be explained without loss of other benefits. Individuals already using LLINs will be encouraged to continue usage. Informed consent will be read, and consent forms signed and dated by participants. One copy of the form will be given to the household to keep for personal records, and one copy will be kept in the project files. If a participant is unable to sign the consent form, a fingerprint will be taken.

When the information is read to the family, they will be given a consent form, translated into Swahili, to read before signing. The form has been designed to give full disclosure in a format that is easy to comprehend. The language in the form is simple and aimed at a primary education level to ensure every member of the target group will be able to understand it. The field worker will be trained to ask whether the household understands all information in the form, or whether any sections need clarification.

### Enumeration of consenting households

Mapping/census of the study area will be conducted in the baseline period to update maps and add new households to the database. The census will record (a) the Global Positioning System (GPS) coordinates; (b) head of household; (c) number of occupants (adults and children); (d) number of bedrooms and total number of rooms; (e) number of sleeping places; (f) number and type of LLINs; (g) predominant wall material; and (h) predominant roof material.

Every building within each hamlet will be mapped using a GPS handheld unit (Garmin Legend e-trex) and ExpertGPS v3.8 (TopoGrafix) software. Cluster boundaries, health facilities and other landmarks will also be geo-located. Each house will be assigned a unique 8-digit household identification (ID) consisting of 3-digit village code, 2-digit hamlet code and 3-digit house code.

### Indoor residual spraying and quality control

Consenting households HHs in the intervention arm will be sprayed with VECTRON™ T500 (100 mg of AI/m^2^), those in the reference arm will receive IRS with Fludora® Fusion (200 mg/m^2^). Prospective spray operators will undergo a medical examination; those with underlying health problems will be excluded. Pregnant women will also be excluded. Spray operators recruited from the clusters will be trained according to WHO guidelines. A total of 100 spray operators will be recruited to conduct the IRS campaign, 5 from each cluster. All sleeping and living rooms in consenting houses will be sprayed, whilst kitchens and storerooms will be excluded. All walls will be sprayed and ceilings will also be sprayed, if accessible. Furniture will be removed from houses and inhabitants will be asked to remain outside during spraying and for 2–3 h afterwards.

Spray operators will be provided with personal protective equipment and clothing and health checks will be performed on them before and after spraying. If operators experience any adverse events, they will receive free medical care and the effects will be documented.

Chemical analysis of the insecticide dosages applied to the walls will be carried out as a quality control of the IRS application process. Whatman® No. 1 filter papers will be attached to the walls of HHs before spraying and then removed post-spray. Four filter papers will be used per HH on different walls, in 20 randomly selected HHs per cluster.

### Intervention monitoring

#### Vector density

CDC light traps hung inside houses next to occupied LLINs will be used to collect mosquitoes for species identification, sporozoite ELISA, and characterization of DNA-based resistance mechanisms. Four operatives will be allocated with 5 light traps each and given responsibility for trapping in 4 of the 16 clusters. In each cluster in each month there will be 3 rounds of light trap collections spaced over 3 weeks in 15 randomly selected HHs. Therefore, in each treatment arm of 8 clusters there will be 120 light trap nights in each month. All households in each cluster will be re-randomised at each monthly surveillance point. Therefore, in each cluster there will be 180 light-trap nights spread across the 12-month post intervention period, from which non-inferiority will be determined. All mosquitoes collected will be identified morphologically to genus and species complex level (*An. gambiae s.l.*, *An. funestus s.l.* and *Culex* spp.). Sub-samples taken from each cluster each month will be identified to species level using molecular diagnostic assays; numbers and proportions identified will depend on the total numbers caught.

#### Phenotypic insecticide resistance testing

WHO bottle bioassays with 1 h exposure [29] will be used to determine phenotypic resistance of wild *Anopheles* mosquitoes to broflanilide (6 µg/bottle), deltamethrin (12.5 µg/bottle) and clothianidin (90 µg/bottle). Drawing on CDC methods regarding the coating of Wheaton bottles [30], the above-mentioned diagnostic concentrations of these insecticides have been shown to kill 100% of insecticide susceptible mosquitoes. Broflanilide will be coated together with MERO 800 ppm/bottle. Insecticide solutions will be prepared from technical grade material dissolved in acetone.

*An. gambiae s.l.* and *An. funestus s.l.* will be collected as larvae from breeding sites within the study area and reared in the insectary. Progeny of these wild *An. gambiae s.l.* and *An. funestus s.l.* will then be exposed to insecticide according to standard operating procedures [29]. Knockdown will be recorded for all insecticides after 1 h and mortality will be recorded after 24 h for deltamethrin, and 72 h for broflanilide and clothianidin. Assays will be conducted at three timepoints: before IRS, at 3 months post-spraying, and at the end of the field study (12 months post-spraying) to detect whether there have been any changes in insecticide susceptibility in wild *Anopheles* populations resulting from exposure to the IRS. WHO bioassays will also be performed with *An. gambiae* s.s. Kisumu (pyrethroid-susceptible strain) and *An. gambiae* s.s. Zeneti or Muleba-Kis (pyrethroid-resistant strains) colonies for comparison and quality control.

#### Genotypic insecticide resistance monitoring

For individual mosquitoes, morphologically identified as *An. gambiae* s.l. [31], DNA will be extracted from legs/wings and used for species identification and detection of L1014S-kdr, L1014F-kdr and G119S-ace1 [17, 32, 33]. Sporozoite detection (CSP-ELISA) will be performed on a subset of PCR-confirmed *An. gambiae* s.s. and *An. arabiensis* [34]. Separate pools of 5 individuals, PCR-confirmed as either *An. gambiae* s.s. or *An. arabiensis*, will be prepared and RNA extracted. cDNA will be synthesized and metabolic gene expression measured relative to susceptible *An. gambiae* s.s. and *An. arabiensis* colony strains; CYP6M2, CYP6P3, CYP6P4, CYP66Z3, CYP9J5 and CYP9K1 will be measured in *An. gambiae* s.s. and CYP6AA1, CYP6AA2, CYP6P15P, CYP6P1, CYP6AD1, COE_4679, CYP6P3, CYP6P4 and 15,786 (ester hydrolase) in *An. arabiensis* [35].

For individual mosquitoes, morphologically identified as *An. funestus* s.l. [31], DNA will be extracted from legs/wings and used for species identification and detection of L119F-GSTe2, CYP6P9a and CYP6P9b. Sporozoite detection (CSP-ELISA) will be performed on a subset of PCR-confirmed *An. funestus* s.s. Separate pools of 5 individuals, PCR-confirmed as *An. funestus* s.s., will be prepared and RNA extracted [31, 36–39]. cDNA will be synthesized and metabolic gene expression measured relative to a susceptible *An. funestus* s.s. colony strain; CYP6N1, CYP6M7, CYP6M1 and CYP6Z3 will be measured [36].

#### IRS residual activity

WHO cone bioassays on IRS treated walls of houses will be used to assess residual activity in both trial arms at monthly intervals until the end of the trial 12 month post-IRS intervention [40]. Plastic WHO cones will be fixed to four walls per house placed in a diagonal arrangement across the room, and one additional cone will be fixed to an outside untreated wall to act as a control. Of the four selected households per cluster, two will be constructed out of cement and the other two out of mud, to compare substrate materials. To determine IRS product efficacy both pyrethroid susceptible and pyrethroid resistant strains will be used. In each cone test, 10 *An. gambiae* s.s. mosquitoes [40] will be aspirated into each cone and exposed for 30 min. After exposure, mosquitoes will be held in paper cups with cotton wool soaked in 10% glucose solution. Immediate knockdown and delayed mortality at 24, 48 and 72-h will be scored. Susceptible and resistant mosquitoes will be tested in the same room on alternate days according to availability. The pyrethroid resistant *An. gambiae* s.s. Zeneti strain possesses the L1014S-kdr mutation and elevated oxidases levels conferring metabolic resistance. If wild *An. gambiae* s.s. are in short supply, adult F1 of *An. funestus* s.l. or *An. gambiae* s.s. Muleba-kis will be laboratory-reared for monthly residual bioassays. With 4 test houses per cluster, and 4 cone tests per house, up to 160 susceptible and 160 resistant mosquitoes will be tested per cluster per month.

### Operational safety and community acceptance

#### Safety

The health status of spray men will be examined before and after spraying by qualified medical staff. Spray men will be asked to complete a questionnaire immediately after spraying has finished and then one month later to determine what, if any, adverse events they may have experienced and at what frequency. Similar questionnaires on adverse events will also be distributed in the community after spraying. Study participants will also be encouraged to contact members of the study team if they experience health issues that they believe are related to the IRS.

An independent IRS human safety assessment for VECTRON™ T500 will be conducted by Environmental Resources Management (ERM) according to the terms of the ‘WHO Generic risk assessment model for indoor residual spraying of insecticides' [41]. According to the risk assessment report, the insecticide is non-mutagenic and non-genotoxic, shows low levels of mammalian toxicity, and at the application rate proposed (100 mg/m^2^) poses acceptable risk of exposure to professional spray operators and to adult residents sleeping in treated houses; this being about 30-fold and 100-fold lower than the acceptable daily intake, respectively, using the WHO model [42].

#### Acceptability

Questionnaires on the ease of insecticide application will be given to all spray operators while questionnaires on community acceptability will be given to a random sample of two clusters per study arm immediately post-spraying and then repeated with the same sub-sample after 6 months.

Focus group discussions (FGDs) will be carried out with a subsample of community participants (8 participants in each FGD) in two randomly selected clusters in each arm. These will be performed six months post-intervention. Within these discussions, factors such as perceived adverse events, benefits, supplementary usage of nets and other means of mosquito protection will be explored and discussed.

